## Abstract

**Background:**

The prevalence of depression in young people is increasing. The predominant co-morbidities of juvenile depression include sleep disturbances and persistent problems with the sleep-wake rhythm, which have shown to influence treatment outcomes negatively. Severe mood dysregulation is another condition that includes depressive symptoms and problems with the sleep-wake rhythm. Patients with severe mood dysregulation show symptoms of depression, reduced need for sleep, and disturbances in circadian functioning which negatively affect both disorder-specific symptoms and daytime functioning. One approach to treating both depression and problems with the sleep-wake rhythm is the use of light therapy. Light therapy is now a standard therapy for ameliorating symptoms of seasonal affective disorder and depression in adults, but has not yet been investigated in children and adolescents. In this trial, the effects of 2 weeks of morning bright-light therapy on juvenile depression and severe mood dysregulation will be evaluated.

**Methods/design:**

A total of 60 patients with depression, aged between 12 and 18 years, in some cases presenting additional symptoms of affective dysregulation, will be included in this trial. Morning bright-light therapy will be implemented for 2 weeks (10 sessions of 45 minutes each), either with ‘active’ light (10,000 lux) or ‘inactive’ light (100 lux). A comprehensive test battery will be conducted before and after treatment and at follow-up 3 weeks later, to assess depression severity, sleep, and attention parameters. Melatonin levels will be measured by assessing the Dim Light Melatonin Onset.

**Discussion:**

In this pilot study, the use of morning bright-light therapy for juvenile depression and severe mood dysregulation shall be evaluated and discussed.

**Trials registration:**

Current Controlled Trials ISRCTN89305231

## Background

Major depressive disorder (MDD) is one of the most prominent health problems affecting mood as well as mental and physical conditions. About 1 out of 10 adults experiences affective disturbances and a loss of interest, the core symptoms of depression [1]. Behavioral and cognitive difficulties, including memory or attention problems, changes in eating behavior, and persistent sleep disturbances, have been reported [2-4]. Effective treatment strategies for MDD in adults include antidepressant medication, psychotherapy, or a combination of both [5]. In adolescents, prevalence rates for MDD, also called juvenile depression in this group, are about 4 to 8%, and the rate seems to be increasing [6]. This relatively high rate is of particular interest for two reasons.

First, the presentation of MDD in young people might be different from that in adults. However, there are many symptoms common to both groups, including irritability, low frustration tolerance, violent temper, and externalizing and histrionic behavior [7]. These symptoms can lead to serious negative psychosocial consequences, including impaired academic and occupational functioning, high-risk sexual activity, and social difficulties [8]. Moreover, the predominant symptoms of juvenile depression implicate sleep disturbances and persistent problems with the sleep-wake rhythm [9,10], which are present in about 75% of adolescents with depression [11].

Second, treating juvenile depression is difficult. The available treatments have substantial shortcomings, and remission rates of moderate to severe depression are low [12,13]. Although cognitive behavioral therapy (CBT) is the treatment of choice for mild depression, CBT alone might not be sufficient in more severe cases. Several randomized controlled trials (RCTs) have indicated no or only small differences between pharmacotherapy with a selective serotonin reuptake inhibitor (SSRI), psychotherapy, and placebo (for an overview, see the American Academy of Child and Adolescent Psychiatry website [14]). Combination trials of both SSRIs and psychotherapy, a treatment that is commonly implemented in clinical practice, have not shown superiority to treatment with either therapy alone, and remission rates have been reported to be less than 40% [14,15]. Another important point is that treatment research has primarily focused on acute treatment, whereas early-onset depression is often chronic and recurrent. One influencing factor might be the presence of co-occurring sleep disturbances, which often remain as a residual symptom even after successful acute treatment [13]. These problems with the sleep-wake rhythm have been suggested to be a robust risk factor for the development of both the first depressive episode and recurrent episodes [1]. Sleep disturbances and insomnia presenting in juvenile depression are associated with higher depression severity, greater fatigue, and higher rates of suicidal behavior [16]. Emslie *et al*. noted in two large, double-blind RCTs [17] that sleep disturbances may negatively affect treatment response, as adolescents receiving treatment with the SSRI fluoxetine were less likely to respond to the treatment if they also had sleep disturbances. Based on these results, it is essential that sleep disturbances are adequately assessed and co-treated consistently along with the depression. However, there is as yet no evidence-based treatment for insomnia in adolescents with depression [17].

One possible non-pharmacological treatment approach for ameliorating depressive symptoms and co-occurring sleep disturbances is morning bright-light therapy, which has been used successfully for adults [18,19]. Light therapy has primarily been studied in patients with seasonal affective disorder (SAD) and has been shown to have good efficacy in ameliorating depressive symptoms in this subgroup. In adults with SAD, Lam *et al*. [20] reported that light therapy was as efficient as antidepressant treatment with fluoxetine, but had a faster onset of action and fewer side effects. The effects of light therapy are apparent after about 1 week of treatment [21], and remission rates of up to 80% have been reported for SAD [22]. In addition, Even and colleagues [19] carried out a systematic review based on 15 studies, and reported efficacy of light therapy as an adjuvant treatment to antidepressants in non-seasonal depression as well. However, they concluded that the evidence for the effects of light therapy alone (without antidepressant) was still inconsistent [19].

Light therapy has also been shown to be effective for other symptoms besides depression. For example, it may induce stabilization of the circadian rhythm (the biological rhythm controlling the sleep-wake cycle) and thereby, improve difficulties with sleep onset and difficulties sleeping through the night [23]. This is of particular interest because an intimate relationship between sleep and emotion regulation has been reported [24], with the consequences of disturbed sleep including symptoms such as heightened impulsivity and aggressive behavior. Preliminary evidence indicates that light therapy has a positive influence on behavior, irritability and attention parameters [25-27]. Furthermore, it has been suggested that, independent of specific diagnoses, the severity of psychiatric symptoms increases and long-term outcomes worsen when circadian disturbances are present [28], reinforcing the crucial relationship between sleep and regulation of emotions. Therefore, it is reasonable to assume that light therapy might be a useful method of stabilizing circadian functioning and thereby inducing more general improvements on emotional regulation. Despite these positive results in adults, there have only been very few studies investigating light therapy for adolescents. One RCT of children and adolescents with SAD showed that 1 week of light therapy significantly decreased parent-rated depressive symptoms [29]. A more recent 1-week trial of light therapy as an adjunctive treatment for young people with mild depression showed significant improvements in depression scores on the Beck Depression Inventory (BDI) from baseline to the end of therapy in the active treatment group [30]; however, participants received concomitant CBT and pharmacotherapy during the trial, which may have led to additional positive effects.

One phenotype that has a high prevalence rate in clinical populations and that elicits considerable problems with emotional regulation, depression, and circadian disturbances is severe mood dysregulation (SMD). Children and adolescents with SMD show severe affective and behavioral dysregulation, including irritable mood, hyperarousal, and increased reactivity to negative emotional stimuli [31,32]. Characteristics of SMD include not only depressive symptoms that might develop into MDD later on [33], but also circadian dysfunctions such as reduced need for sleep, disturbances in sleep continuity at sleep onset and through the night, lower sleep efficiency, reduced rapid eye-movement (REM) sleep and impaired daytime behavior, which have consistently been reported [34-36]. The initial treatment approaches, similar to those for pediatric bipolar disorder and attention deficit hyperactivity disorder (ADHD), include mood stabilizers and stimulants, and have shown some positive effects [37,38]. A novel psychosocial treatment with CBT indicated improvements in depressive symptoms, mood lability, and global functioning [39]. Although these initial treatment approaches were reported to have some positive effects on SMD symptoms, children and adolescents with SMD and additional ADHD were more likely to remain significantly impaired than those with only ADHD after a 3-week combination trial with stimulants and behavior modification therapy [37]. Therefore, a wider range of treatment approaches for SMD is needed, as those that have been evaluated to date have shown only limited improvements. It is possible that, as in juvenile depression, circadian disturbances might be an influencing factor on treatment outcome in SMD. Considering that preliminary results of light application besides SAD and MDD have shown positive influences on affective and behavioral regulation and on circadian functioning, light therapy might constitute a reasonable co-treatment for SMD symptoms as well [40].

The proposed study is an RCT of bright-light therapy in juvenile depression. We plan to enroll 60 adolescents with depression. We hypothesize that 2 weeks of morning bright-light therapy will improve depressive symptoms and additional sleep disturbances in these adolescents. On an exploratory basis, the study will additionally evaluate the outcomes of morning light therapy on SMD symptoms.

## Methods/design

### Participants and recruitment

Participants of this study will be recruited from the inpatient unit of the LWL (University Hospital Hamm, Ruhr University Bochum, Germany), a tertiary-care hospital for child and adolescent psychiatry. The hospital provides child psychiatric care for a population of 1.6 million inhabitants, covering both urban and rural areas, and is the sole provider of inpatient care serving the study area.

All patients between 12 and 18 years who are referred to the hospital will be screened consecutively for participation. Patients with moderate or severe depression (according to the International Classification of Diseases, version 10; (ICD-10), based on parent and child interviews and assessed using the second edition of the BDI (BDI-II [41]), will be included in the trial. Diagnoses will be confirmed using the Diagnostic Checklist for Depressive Disorders [42] conducted by a clinical psychologist or child psychiatrist. Presence of co-morbid disorders will be allowed, excluding bipolar 1 disorder and schizophrenia. The specific eligibility criteria of the study are listed in Table 1.

**Table 1 T1:** Eligibility criteria

Inclusion criteria	Moderate to severe depression (ICD-10/BDI-II)
	Being 12 to 18 years of age
	Ability to understand character and individual consequences of the trial
	Written informed consent of the person with primary custody must be available before enrolment in the trial
Exclusion criteria	Acute suicidal tendencies
	Treatment with antidepressants
	Treatment with beta-blockers
	Treatment with high-potency neuroleptic drugs
	Diagnosis of bipolar 1 disorder or schizophrenia
	Diseases of the eye with involvement of the retina
	Pregnancy or lactation

BDI-II, Beck Depression Inventory, second edition; ICD-10, International Classification of Diseases, version 10.

#### Ethics and written consent

The study has been approved by the medical ethics committee of the Ruhr-University Bochum, Germany (registration number 3996–11), and will be conducted in accordance with the Helsinki Declaration. Before entering the study patients will be informed about the study objectives, study design, and potential risks by one of the main investigators and will also receive this information in writing. Patients will be informed about their right to withdraw from the study at any time. Written consent will be obtained from the persons in charge with primary custody. After informed consent is obtained, the therapist in charge will be informed by mail about the patient entering the study.

#### Randomization and blinding

After screening, patients will be randomized and allocated to either the active light intervention (experimental group; 10,000 lux) or to the inactive light intervention (control group; 100 lux). Randomization will be carried out by randomly drawing group allocations by hand from a randomizer box in which the number of possible group allocations is equal. For practical reasons, the primary investigator of the study who is performing the randomization and delivering the treatments (but is not involved in outcome ratings) will be aware of the participants´ allocation, but all therapists on the patients´ units will be blinded to the allocation groups.

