#### Time points of assessments

The assessment time points are as follows.

•T1: The initial assessment for eligible patients will be carried out after about 1 week of care in the unit. At this point, patients will have become used to being in the hospital, and will probably have a more regular day and night rhythm.

•T2: After 2 weeks of morning light-therapy intervention, there will be a comprehensive post-therapy assessment.

•T3: One week later, depression severity will be assessed to monitor changes.

•T4: Another week later, there will be another assessment of depression severity.

•T5: Three weeks after the light-therapy interventions have ended, another comprehensive assessment will be carried out.

An overview of the timeline of the study is shown in Figure 2.

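### Allocation concealment is not secured: the unblinded investigator who delivers the light also draws the allocations by hand from a box

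*Protocol article*

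**What the plan says.** The protocol article, under the heading on randomization and blinding, fixes the mechanism: "Randomization will be carried out by randomly drawing group allocations by hand from a randomizer box", with equal numbers for the two arms in the box. It names the operator as "the primary investigator of the study who is performing the randomization and delivering the treatments", gives practical reasons for the arrangement, and adds that this person "will be aware of the participants´ allocation, but all therapists on the patients´ units will be blinded to the allocation groups". The same sentence keeps this investigator out of the outcome ratings.

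The timing is given as "After screening, patients will be randomized and allocated to either the active light intervention". Under the assessment time points, T1 is described thus: "The initial assessment for eligible patients will be carried out after about 1 week of care in the unit". The ethics and consent section has patients informed before entry "by one of the main investigators", without saying whether that is the person who draws.

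The article does not say whether drawn slips go back into the box. It mentions no independent holder of the sequence, no sealed container, no log of draws and no rule against redrawing.

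**The concern.** An article may leave operational detail to the full protocol. Here, however, the article states the method and the operator, and it puts three things in one pair of hands: drawing the allocation, delivering the treatment, and knowing all previous allocations. Random assignment protects the comparison only if the decision to enter a patient cannot respond to the allocation. With this arrangement, an unwelcome slip could be replaced, or an entry could be held back, and nothing described would leave a trace.

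The risk is selection bias: patients who differ in likely response end up unevenly spread between 10,000 lux and 100 lux. With 60 patients planned, there are few allocations over which such differences could average out.

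**Working it through.** The article gives no figure for concealment or predictability, so there is none to reproduce. Its sample-size figure (54) is not an input to the argument and enters only as an alternative box size.

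**Inputs.** Planned enrolment is 60 (end of the Background section). The arms are equal in number (randomization section; the control-group section assigns half the patients to control). *Assumption:* the box starts with 30 + 30 slips. The article states equality but not the count.

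**1. Redraw.** Let p be the chance that a draw gives the preferred arm. If one unwanted slip is put back and the draw repeated, the chance is 1 − (1 − p)². With p = 0.5 this is 1 − 0.25 = 0.75. If the unwanted slip is set aside instead, the first redraw from 30 + 30 gives 0.5 + 0.5 × 30/59 = 0.754. The result is about 75% whether or not slips are normally returned.

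**2. Anticipation, slips not returned.** A person who knows past allocations guesses the arm with more slips left. For n + n slips, the expected number of correct guesses is n + (4ⁿ/C(2n, n) − 1)/2, and the expected number of allocations certain at the end is 2n/(n + 1).

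- n = 30: 4³⁰/C(60, 30) = 9.749, so 30 + 8.749/2 = 34.37 of 60, or 57.3% against 50% by chance. Certain at the end: 60/31 = 1.94 allocations on average.
- n = 27 (a box of 54): 31.13 of 54, or 57.6%.

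The gain is uneven. Computed position by position for 30 + 30, the correct-guess rate is about 53% over the first 30 patients, 62% over the second 30, 70% over the last 10 and 77% over the last 5.

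**3. Anticipation, slips returned.** Each draw is then 50:50 and nothing can be predicted from a count. The cost is possible inequality of the arms: from Binomial(60, 0.5), a split of 35:25 or worse has probability 24.5%, and 36:24 or worse 15.5%. This is not a bias. A 35:25 split keeps 4 × 35 × 25/60² = 97% of the efficiency of 30:30.

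**4. Would small blocks help?** The treating investigator would still see past allocations. The formula in step 2 gives, per block:

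- Blocks of 4 (n = 2): 2 + (16/6 − 1)/2 = 2.83 of 4, or 70.8%.
- Blocks of 6 (n = 3): 3 + (64/20 − 1)/2 = 4.10 of 6, or 68.3%.

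Both are more predictable than the box (57.3%), so small blocks are not the remedy here.

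**The case against.** The strongest reply is that a blind draw does conceal the next slip, and that redrawing presumes conduct the article nowhere describes. The first half stands: a reader might infer that allocation is open or known in advance, and the text does not support that. The second half does not answer the point, because concealment procedures exist so that nobody has to rely on the conduct of an unblinded operator.

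Other protections are real but aimed elsewhere. Unit therapists and CGI raters are blinded, which limits detection bias. Screening is consecutive, which narrows the room for steering but leaves the time of entry and the draw itself open. Adjustment for baseline BDI-II deals with measured severity at T1, so it would be too strong to say that analysis can correct nothing. It cannot reach unmeasured differences.

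Two further inferences should be resisted. A reader might conclude that allocations can be anticipated outright; that needs slips not to be returned, which the equal numbers suggest but do not state, and even then the average gain is 7 percentage points. A reader might also conclude that baseline is measured after allocation, since randomization follows screening and T1 comes after about a week on the unit. No sentence puts T1 after the draw, and the flow chart and time schedule are not available here. Nor does the consent section show that the person informing patients is the one who draws.

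Finally, no bias in the treatment effect has been computed: a guessing rate is not a bias.

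**Conclusion.** The point holds as a weakness of the stated method: allocation concealment is not secured. The main exposure is an undetectable redraw (50% to 75% for a preferred arm on the occasion it is used) or a deferred entry, and it does not depend on whether slips are returned. The tally advantage is secondary: about 57% over 60 patients, conditional on 30 + 30 slips drawn without return, and concentrated late in recruitment. The documents do not show that any allocation was or will be steered, and the size of any resulting bias cannot be derived from them. The pilot label does not dispose of the matter, because the article plans a two-sided test at 5% with 80% power. The order of T1 and allocation needs clarification; it is not a demonstrated error.

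**What to change.** 1. Have a hospital colleague with no role in enrolment or treatment generate and hold a computer-generated 1:1 sequence. Do not use small blocks; use one permutation (30 + 30 for a full trial) or large blocks whose size is not disclosed to the investigator.
2. Release each allocation by sequentially numbered, sealed, opaque envelope or by telephone, only after eligibility, consent and the T1 BDI-II have been recorded.
3. Keep a dated log of every release.
4. State explicitly that T1 precedes allocation.
5. The trial is listed as ongoing, so apply this to the remaining patients and report the method used for those already allocated.

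The same investigator can still deliver the light, and the sample size, devices and assessments are unchanged. The cost is a small amount of a colleague's time and a change of procedure mid-trial.

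One limit should be acknowledged. A treating investigator who knows the list length can still keep a tally, and a shorter list is slightly more predictable: with 30 patients left (15 + 15), the formula gives 17.96 of 30, or 59.9%. What the change secures is that a patient's entry is fixed before the allocation is seen, that no allocation can be redrawn, and that the order of releases can be checked.

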### Interventions

Interventions will be conducted following the protocols described by Wirz-Justice *et al*. [43]). Based on empirical evidence indicating good results for light therapy with a duration of 7 to 14 days for non-seasonal depression [18,19], two parallel interventions will be created, each lasting 2 weeks, and will be conducted in the mornings, in addition to usual treatment in the respective treatment units.

#### Experimental group

Patients randomly allocated to the experimental group will receive 2 weeks of active morning light therapy with 10,000 lux at eye level in gaze direction (LD 110^®^; DAVITA^®^ Medizinische Produkte GmbH & Co. KG, Kleve, Germany), with each session lasting for 45 minutes. The therapy will start about 7.5 hours after the estimated individual dim light melatonin onset (DLMO), estimated by the Morningness-Eveningness-Questionnaire (MEQ) [44]), as it has been shown that by administering light at that time point, the efficacy of light therapy is increased [22].

#### Control group

A valid placebo group will be created by randomly assigning half of the patients to the control group to receive 2 weeks of inactive light therapy not exceeding 100 lux at eye level in gaze direction (Luxor LED light alarm clock, lowest level; DAVITA^®^ Medizinische Produkte GmbH & Co. KG, Kleve, Germany), with each session lasting for 45 minutes. Each session will commence about 7.5 h after the estimated DLMO to parallel the experimental group.

Finding an appropriate control group for light therapy to minimize placebo effects is difficult, because these effects are expected to be relatively high [19,45,46]. To design conditions that the patients will not consider a control group, we have chosen professional light-therapy devices for both groups, adjusting the lux levels respectively. To control for possible expectation bias, both groups will be instructed that the aim of the study is to compare two different types of light therapy. Moreover, to minimize bias, the therapists on the respective units will be informed that the light therapy for both groups is active.

To ensure that an appropriate and constant number of lux is administered in each group, intensities will be quantified using a lux meter (PCE-172; PCE Instruments, Meschede, Germany). The light intensity that will be used in this study lies within the range of normal daylight exposure. Its long-term ocular safety has been shown in patients with SAD who received bright-light therapy at an illuminance level of 10,000 lux [47].

During the interventions, patients will be allowed to have breakfast or read magazines and books with neutral content (for example, magazines containing plain information without emotionally arousing material). To ensure that every participant has received the same amount of light therapy at the end of the treatment period, treatment can be prolonged for up to 1 day if a patient misses a light-therapy session for some reason (for example, somatic illness). If a patient misses more than two sessions, he/she will be excluded from the study. In total, about three patients can be treated in parallel within each group (see Figure 1 for a flow chart of the study).

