#### Statistical analyses

Data will be assessed using SPSS software (version 20; SPSS Inc., Chicago, IL, USA). Correctness of the data will be assured by double-entry of the data. Data will be analyzed according to both intention-to-treat (ITT) and per-protocol (PP; efficacy population) principles. ITT will assess all randomized patients, while PP analyses will assess patients who receive 2 weeks of morning light therapy with no violation of the study protocol.

All planned comparisons will compare T2 to T5 relative to T1. The primary endpoint of the study is change in depressive symptoms (BDI-II total score) during the trial. Baseline depression level (that is, BDI-II total score at T1) will be controlled for in the two-factor repeated-measures ANCOVA. This model accounts for differences between groups at baseline. Furthermore, the study will evaluate whether the effects of morning light therapy on mood might partly be mediated by its effect on the circadian rhythm, and will be assessed by questionnaires and saliva samples. For missing values, the multiple imputations (MI) technique will be used, because a recent meta-analysis for RCTs in obesity found this to have modest superiority to fitting mixed linear models or using last observation carried forward (LOCF) methods [76]. With the MI technique, plausible values for the missing data are imputed. Each of the datasets is then analyzed separately using the desired model (in this case, the two-factor repeated-measures ANCOVA). With this parameter, estimates are made for each of the datasets, and these are then combined using standard rules for MI analyses [77,78]. These combined parameter estimates can then be used for hypothesis testing and for making inferences. In this RCT, two-factor repeated-measures ANCOVA will be used with group as between-subject factor and time as within-subject factor (T1 to T5). In cases of significant correlations with the primary endpoint, covariates will include baseline BDI-II score, gender, intelligence, seasonality, and circadian preference. The 95% confidence intervals and pre-post effect sizes will be derived for each analysis. All tests of statistical significance will be interpreted with a criterion of *P* < 0.05, two-sided.

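### Excluding randomised patients from the study for missed sessions conflicts, read literally, with an intention-to-treat analysis of everyone randomised and may leave their outcomes wholly imputed

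*Protocol article*

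**What the plan says.** All references are to the protocol article.

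- **Randomization and blinding:** "After screening, patients will be randomized and allocated to either the active light intervention" or to the inactive one. Allocation therefore comes before the first session.
- **Methods/design (abstract):** ten sessions of 45 minutes over two weeks.
- **Control group (under Interventions):** a missed session can be made up, since "treatment can be prolonged for up to 1 day if a patient misses a light-therapy session for some reason". Beyond that, "If a patient misses more than two sessions, he/she will be excluded from the study".
- **Time points of assessments:** T1 precedes treatment, T2 follows the two treatment weeks, T3 and T4 come at weekly intervals, and T5 is three weeks after treatment ends.
- **Statistical analyses:** "Data will be analyzed according to both intention-to-treat (ITT) and per-protocol (PP; efficacy population) principles". The two sets are then defined: "ITT will assess all randomized patients", whereas "PP analyses will assess patients who receive 2 weeks of morning light therapy with no violation of the study protocol". On incomplete data, "For missing values, the multiple imputations (MI) technique will be used".

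The article does not say whether exclusion means from treatment, from follow-up or from one analysis set. Nor does it say whether an excluded patient is still assessed at T2 to T5.

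**The concern.** The missed-session rule acts on something that happens after randomisation and that treatment may influence. If exclusion ends a patient's assessments, the intention-to-treat analysis loses observed outcomes for the patients in whom adherence failed. Imputation then has to stand in for data that could have been collected.

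Three features of the plan add to this:

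- The investigator who randomises and delivers the sessions knows the allocation, and the article does not say who applies the exclusion.
- Adverse events are asked about at assessments. If assessments stop, events that led to the missed sessions may go unrecorded.
- The Discussion names feasibility and acceptance among the aims of the pilot, and patients who miss sessions are the most informative on acceptance.

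The rule governs data collection, so this cannot be left to a later analysis plan. No analysis recovers a BDI-II that was never taken.

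**Working it through.** **1. When the rule acts.** More than two missed means three or more of the ten planned sessions. The third miss can happen at the tenth session at the latest, or on the one-day extension. T2 comes only after treatment, so the threshold is always crossed before T2.

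**2. What is then observed.** The repeated-measures model uses T1 to T5. A patient excluded during treatment and not followed has T1 only, so 5 − 1 = 4 of the five BDI-II values are missing, including every value after baseline.

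**3. What imputation can do with that.** With only T1 and other baseline data, imputed values are drawn from the pattern among patients who continued, given whatever arm and baseline terms the imputation model contains. This is valid if, given those terms, excluded patients would have done as well as those who stayed. It fails if sessions were missed because of side effects, lack of benefit or worsening mood that baseline does not predict. Such a patient also adds little information on the treatment difference, so the result moves towards an analysis of those who stayed.

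**4. Room in the sample size.**
- The plan's figure is 54 in total for 80% power, two-sided α = 0.05. A two-sample t-test with d = 0.78 gives 27 per arm, 2 × 27 = 54, which reproduces it.
- Enrolment is 60. The margin is 60 − 54 = 6, and 6/60 = 10%.
- No exclusion or dropout rate is stated, so the loss fractions below are assumptions. Power is for the same test at d = 0.78, if excluded patients contribute no outcome information.

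| Assumed loss | Patients with outcomes | Power |
|---|---|---|
| 0% | 60 | 84.4% |
| 10% | 54 | 80.3% |
| 15% | 51 | 77.9% |
| 20% | 48 | 75.3% |

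The value 0.78 is used only because it reproduces the stated 54. The point does not depend on it.

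**5. Bias.** Let p be the proportion excluded in an arm and g the amount, in SD, by which the excluded do worse than their imputed values. If g is the same in both arms, the bias in the group difference is (p_active − p_control) × g. The document supplies neither quantity. Under assumed inputs:
- equal exclusion in both arms: 0 × g = 0
- 15% against 5%, g = 0.5: 0.10 × 0.5 = 0.05 SD
- 20% against 5%, g = 0.75: 0.15 × 0.75 = 0.11 SD

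Swapping the arms reverses the sign. These figures show how the bias would arise and are not estimates for this trial.

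**The case against.** The strongest reply is that the two sections are meant to be read together. The missed-session rule would then simply feed the split between the two analysis sets, and excluded patients would remain in the intention-to-treat set. The article condenses a fuller protocol and its flow chart is not shown, so follow-up of these patients may be settled there. It is a pilot, and multiple imputation is already planned. The only example given for a missed session is somatic illness, which need not differ by arm.

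Much of this stands. A reader might infer that the promised intention-to-treat analysis cannot be done. The document does not support that: all randomised patients can be kept in the set with T1 observed and the rest imputed. A reader might also infer that assessments certainly stop at exclusion, but the article does not say so.

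A further tempting inference is that running two analysis sets without ranking them inflates the type I error. Nothing in the article says that success in either set suffices, and the ranking is commonly left to an analysis plan. That is no part of this point.

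What the reply does not remove is the wording. The rule says from the study, when a per-protocol set for departures already exists. Staff who follow it as written could stop collecting the primary outcome.

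**Conclusion.** The point holds as a conflict between two stated rules. Taken at its word, the exclusion in the Control group section is a post-randomisation, adherence-based removal that does not fit an intention-to-treat set of all randomised patients. If excluded patients are not assessed at T2 to T5, their intention-to-treat outcomes rest entirely on imputation from baseline.

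The conclusion rests on one condition that the article leaves open, namely that exclusion ends follow-up. How much harm follows depends on how many patients are excluded, how this differs by arm, and why sessions were missed. None of these is given, so no size or direction of bias can be claimed. The only scale the document offers is the six-patient margin between required and planned enrolment.

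The trial is described as ongoing, so the wording matters now: outcomes not collected under the current rule are lost.

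**What to change.** In the Control group section, replace exclusion from the study with a statement that missing more than two sessions removes a patient from the per-protocol set only. There and in Statistical analyses, add that all randomised patients continue T2 to T5 assessments where consent allows and are analysed in their randomised arm.

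When the rule is moved, the per-protocol definition should also say how one or two missed sessions count. The rule tolerates up to two, the extension is at most one day, and the stated aim is the same amount of therapy for everyone, so these statements need to be reconciled. Which clinical rule applies, and whether light sessions continue for a patient over the threshold, is for the sponsor to decide.

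The cost is a sentence or so in each of two sections and a few additional questionnaire administrations. This is cheap but not free. Patients are recruited from an inpatient unit and questionnaires are completed in the hospital, but T5 falls about 1 + 2 + 3 = 6 weeks into care, and some patients may be discharged before then.
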